## Abstract

**Background:**

Depression, generalized and cardiac anxiety, and posttraumatic stress disorder negatively affect disease severity, participation, and mortality in patients with cardiovascular disease. Psychological treatments within cardiac rehabilitation may improve the outcomes of these patients. We therefore developed a cognitive-behavioral rehabilitation program for patients with cardiovascular disease and mild or moderate mental illness or stress or exhaustion. In Germany, similar programs are well established in musculoskeletal rehabilitation and cancer rehabilitation. However, no randomized controlled trials have evaluated if such programs achieve better outcomes in patients with cardiovascular disease compared with standard cardiac rehabilitation.

**Methods:**

Our randomized controlled trial compares cognitive-behavioral cardiac rehabilitation with standard cardiac rehabilitation. The cognitive-behavioral program complements standard cardiac rehabilitation with additional psychological and exercise interventions. Both rehabilitation programs last for four weeks. We enroll 410 patients with cardiovascular disease and mild or moderate mental illness or stress or exhaustion aged 18 to 65 years. Half of the individuals are randomly assigned to cognitive-behavioral rehabilitation and the other half to standard cardiac rehabilitation. Our primary outcome is cardiac anxiety 12 months after the end of rehabilitation. Cardiac anxiety is assessed with the German 17-item version of the Cardiac Anxiety Questionnaire. Secondary outcomes cover outcomes assessed by clinical examinations and medical assessments and a range of patient-reported outcome measures.

**Discussion:**

This randomized controlled trial is designed to determine the effectiveness of cognitive-behavioral rehabilitation at decreasing cardiac anxiety in patients with cardiovascular disease and mild or moderate mental illness or stress or exhaustion.

**Trial registration:**

German Clinical Trials Register (DRKS00029295, June 21, 2022).

**Supplementary Information:**

The online version contains supplementary material available at 10.1186/s12872-023-03272-1.

## Background

Cardiovascular diseases are the most frequent cause of death and a major risk factor for health-related impairments of activities and participation [1]. About one in three people with a cardiovascular disease has at least one mental disorder in addition to the cardiovascular disease [2]. Persistent psychological impairment in particular increases the risk of mortality of patients with stable coronary heart disease [3, 4], and depression is associated with the degree of disability experienced by long-term survivors of myocardial infarction [5]. Early identification and treatment of psychological impairments is therefore an important objective of cardiac rehabilitation [6–8].

In Germany, cognitive-behavioral rehabilitation was developed for patients coping with a somatic illness who are also affected by psychological stress or comorbid psychological disorders. Cognitive-behavioral rehabilitation is a multimodal intervention that includes additional psychological and exercise interventions as compared to standard rehabilitation programs [9]. In patients with musculoskeletal disorders, randomized controlled trials revealed fewer depressive symptoms in the short and medium term among participants in cognitive-behavioral rehabilitation programs [10, 11] and reported better pain management strategies, lower pain intensity, and better general health following cognitive-behavioral compared with standard rehabilitation programs in the long term [10, 12]. In addition, a propensity-score-matched analysis showed slight benefits of cognitive-behavioral rehabilitation programs implemented in real-world care for patients with musculoskeletal disorders: Participants in cognitive-behavioral rehabilitation reported better self-rated work ability, better physical functioning, better self-management skills, lower pain impairment, and lower fear-avoidance beliefs 10 months after completing the program than comparable individuals receiving standard rehabilitation [13].

In a recent study, we tested the implementation of a cognitive-behavioral rehabilitation program for patients with cardiovascular disease [14]. Study participants were treated in the newly implemented cognitive-behavioral cardiac rehabilitation program or standard cardiac rehabilitation. The additional psychological group intervention was based on acceptance and commitment therapy. Those treated in the cognitive-behavioral program had stronger baseline mental health impairments than participants in the standard cardiac rehabilitation program. In addition, mental disorders were documented more frequently at baseline (especially neurotic disorders, stress disorders, and somatoform disorders). The fidelity of implementation was confirmed. Individuals treated in the cognitive-behavioral program also acknowledged more cognitive-behavioral elements, stronger consistency of the cognitive-behavioral approach, and more gains in competences to cope with the disease. The change in several mental and physical outcomes was substantial and corresponded to large standardized differences between the start and end of rehabilitation. To clarify whether cognitive-behavioral rehabilitation achieves better outcomes than standard cardiac treatment, we consider a randomized controlled trial necessary.

### Objectives

Our randomized controlled trial tests whether participants in the cognitive-behavioral rehabilitation program have more favorable outcomes, in particular mental health outcomes, than participants in standard cardiac treatment. Our primary outcome is cardiac anxiety measured with the Cardiac Anxiety Questionnaire 12 months after the end of rehabilitation [15, 16].

### Trial design

We are conducting a single-center, randomized controlled trial comparing two groups of cardiac rehabilitation patients. The intervention group receives a cognitive-behavioral rehabilitation program. The control group receives the standard cardiac rehabilitation treatment provided at the study center. Participants are randomly assigned to cognitive-behavioral rehabilitation or standard cardiac rehabilitation after giving informed consent.

The study has been registered on the German Clinical Trials Register (DRKS00029295). The items from the World Health Organization Trial Registration Data Set are available as Additional file 1. This paper contains the original study protocol. Any substantial modifications to the study protocol will be submitted to the Ethics Committee of the University of Lübeck for approval prior to implementation. These amendments will be documented in detail in the German Clinical Trials Register and described transparently in trial reports.

The trial is investigator initiated, and the University of Lübeck is the primary sponsor of the trial. An advisory board incorporating researchers, physicians, and employees of Federal German Pension Insurance and the German Pension Insurance North accompanies the conduct of the study and meets once a year.

## Methods

### Study setting

In Germany, rehabilitation due to cardiovascular diseases for people of working age is mainly provided by the pension insurance agencies and is intended to prevent health-related exit from work and disability pensions. Medical rehabilitation is possible both after acute events (e.g., post-acute rehabilitation after an acute myocardial infarction) and due to chronic diseases (e.g., chronic heart failure). There are 115 cardiac rehabilitation departments used by the pension insurance agencies [17], and in 2020, nearly 70,000 cardiac rehabilitations [17] – almost three-quarters of which were post-acute rehabilitations – were completed for people of working age. The utilization of cardiac rehabilitation is almost three times higher among men than women. The average age of patients with cardiovascular diseases whose rehabilitation is covered by the pension insurance agencies is about 55 years. The content of multi-professional cardiac rehabilitation includes exercise therapy (especially aerobic endurance training and strength training), patient and health education, nutrition therapy, psychological and relaxation interventions, and tobacco cessation. In order to ensure uniform and consistent minimum standards throughout Germany, therapy standards for rehabilitation of coronary heart disease have been formulated [18] and are based on the recommendations of the National Guideline for Coronary Heart Disease [19]. The minimum dose specified in the therapy standards for 12 treatment components corresponds to 29 to 34 treatment hours during a three- to four-week rehabilitation program [18]. The rehabilitation center where we recruit patients (https://www.muehlenbergklinik-holsteinische-schweiz.de) is located in northern Germany. It currently has 321 patient treatment slots, 130 of which are for cardiac rehabilitation. Thirty of the 130 treatment slots for patients with cardiovascular diseases are intended for cognitive-behavioral cardiac rehabilitation.

### Eligibility criteria

We are including patients aged 18 to 65 years who receive rehabilitation at our study center due to cardiovascular disease (ICD-10 I05 to I71 as well as I95 and I97) assigned by the Federal German Pension Insurance or the German Pension Insurance North and for whom mild or moderate mental illness or stress or exhaustion are recorded in the application documents for cardiac rehabilitation. For patients assigned by the Federal German Pension Insurance, mental illness or stress or exhaustion is determined by the socio-medical service of the Federal German Pension Insurance. For patients assigned by the German Pension Insurance North, this is determined by a cardiologist at the study center. The determination of mild or moderate mental illness or stress or exhaustion is performed in advance of the program with only the documents used to claim the rehabilitation.

Patients with severe mental illness (schizophrenia, schizoaffective disorder, bipolar disorder, mania, severe unipolar depression), severe heart failure (at least stage III according to the classification of the New York Heart Association), and significant limitations with the German language are excluded.

### Interventions

#### Cognitive-behavioral rehabilitation

The cognitive-behavioral rehabilitation program was developed for cardiac rehabilitation patients with mild or moderate mental illness or stress or exhaustion. The program complements standard cardiac rehabilitation with additional psychological and exercise interventions and follows the framework of cognitive-behavioral rehabilitation formulated by the German Pension Insurance [20].

Cognitive-behavioral rehabilitation is conducted as a group program, i.e., 8–12 patients who begin the rehabilitation program at the same time complete five specific additional cognitive-behavioral components together. Table 1 summarizes these five components, e.g., a psychological group, individual psychological sessions, relaxation training, a seminar on heart and psyche, and an exercise group. Moreover, Additional file 2 provides a detailed description of the five components according to the Template for Intervention Description and Replication [21]. The treatments beyond these five components follow – as in the control group – the recommendations for the rehabilitation of coronary heart disease published by the German Pension Insurance [18]. Cognitive-behavioral rehabilitation lasts for four weeks.

A detailed description of the psychological group can be found in Benninghoven et al. [14]. This group includes seven 90-minute sessions and is based on acceptance and commitment therapy [14, 22, 23]. It combines cognitive-behavioral therapy techniques with mindfulness- and acceptance-based methods and emotion-regulating strategies. In addition to complementary psychological and educational interventions, cognitive-behavioral rehabilitation is characterized by intensified exercise therapy, as there is strong evidence that exercise therapy reduces cardiovascular mortality and hospitalizations and improves quality of life [24].

**Table 1 Tab1:** Components of the cognitive-behavioral rehabilitation program

Brief name	Psychological group	Individual psychological sessions	Relaxation training	Seminar: Heart and psyche	Exercise group
What (procedures)	The seven sessions cover, amongst others, mindfulness exercises, the ACT matrix, acceptance of negative thoughts, mental flexibility, personal values, and the elaboration of concrete plans for the time after rehabilitation. A more detailed overview of the seven sessions is presented in Additional File 2.	During the admission interview, anamnestic information (including contextual factors such as family, work, and biography) as well as the experience of illness and illness behavior are recorded, and the expectations of the rehabilitation patients are clarified. In addition, at the end of rehabilitation, mental disorders are assessed with a standardized short interview in order to specify further treatment recommendations.	Participants learn progressive muscle relaxation and develop individual ways to apply the technique in everyday life.	The following topics will be covered in the two sessions. Session 1: Structure and function of the heart and cardiovascular system; function of the autonomic nervous system and the hormonal system. Session 2: Control function of the brain and influence of the emotional state; influence of lifestyle and attitude changes on physical processes, especially on the cardiovascular system.	The exercise intervention includes an individual admission assessment by a physical therapist, cardiovascular exercise therapy, ergometer training, strength training, and coordination training in a group.
Who provided	A psychological psychotherapist or graduated psychologist in psychotherapy training leads the group throughout the rehabilitation and is the primary psychological contact. The primary physical therapist is present at the first and last group meetings.	Psychological psychotherapist or graduated psychologist in psychotherapy training	Psychological psychotherapist or graduated psychologist in psychotherapy training	Physician	The primary physiotherapist leads the group exercise sessions throughout rehabilitation.
How	Group intervention	Individual intervention	Group intervention	Group intervention	Group intervention
Where	Quiet group room	Workroom of the primary psychologist	Quiet group room/gym	Quiet group room in the rehabilitation facility	Gym
When and how much	During the rehabilitation program, seven sessions of 90 min each, in total 630 min	During the rehabilitation program, at least one 60-minute session	During the rehabilitation program, one session of 60 min and eight sessions of 30 min each, in total 300 min	During the rehabilitation program, two sessions of 60 min each, in total 120 min	During the rehabilitation program, individual admission assessment: one sessions of 30 min, cardiovascular exercise therapy: 20 sessions of 30 min each, ergometer training: one session of 60 min and 11 sessions of 30 min each, strength training: 6 sessions of 60 min each, coordination training: 10 sessions of 30 min each, in total 1680 min

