### Sample size

As a minimum important difference for the 12-month follow-up, we defined 0.2 points of the total cardiac anxiety score (0 to 4 points [15, 16]). Although 0.2 points represent only 5% of the scale range, we consider this small gain to be relevant because we are comparing two comprehensive rehabilitation programs. Assuming a standard deviation of 0.6 points [43], 0.2 points correspond to a standardized mean difference of 0.33. To detect this difference with a two-sided error of 5% and a power of 80%, 286 participants are required. Further assuming a response rate of 70% in the 12-month follow-up, we plan to recruit 410 participants (intervention group: n = 205; control group: n = 205) to be able to detect the minimal important difference also in a complete-case analysis. For our primary intention-to-treat analysis with multiple imputation of missing follow-up scores, a difference of 0.2 points is detected with a power of about 92%.

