### Allocation

Randomization is performed in a one-to-one ratio. The randomization sequence was generated by the principal investigator (MB) using Stata 16.0. Blocks of different size were combined randomly. Allocation concealment is ensured by sealed, opaque, and consecutively numbered envelopes. The envelopes are opened in the study center for randomization only after participants have given informed consent. The group assignment is documented in the study center in the study list through the identification number.

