### Statistical methods

We will analyze short-term (end of rehabilitation and 3-month follow-up) and long-term effects (12-month follow-up) using different models and publish the findings separately. We will use mixed models if more than one measurement point needs to be considered, i.e., end of rehabilitation and 3-month follow-up, and generalized linear models otherwise. If baseline scores are available, these will be included as a covariate when estimating the treatment effect. If outcomes are binary, a logit link will be used. High depression, high generalized anxiety, and high cardiac anxiety, as well as age, sex, and education, are tested as possible moderators of the treatment effect on our primary outcome cardiac anxiety assessed at the 12-month follow-up.

For health economic evaluation, we will calculate an incremental cost-effectiveness ratio [44]. Assessments of costs employ a societal perspective [41, 45]. Effectiveness is measured using quality-adjusted life years as derived from the 12-month assessment of the EQ-5D-5 L [28, 30]. The incremental cost-effectiveness ratio is calculated by dividing the difference in costs between both interventions by the difference in effectiveness between both interventions. Bootstrapping is used to compute a 95% confidence interval of the incremental cost-effectiveness [44].

Missing data will be imputed using chained equations [46]. We will create 20 independent data sets with complete values. Parameter estimates of the models will be combined in accordance with Rubin’s rules [47]. Statistical tests will be regarded as significant if the two-sided p-value of a test is less than 0.05. An up-to-date version of Stata (StataCorp, College Station, Texas, USA) will be used to conduct the analyses.

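### Intervention patients are treated in groups, but the sample size and the 12-month primary model assume independent patients; any positive within-group correlation makes the standard error too small

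*Protocol article*

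**What the plan says.** **Unit of randomization.** Patients are allocated individually (Allocation: "Randomization is performed in a one-to-one ratio").

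**Delivery of the intervention.** The section on cognitive-behavioral rehabilitation says that eight to twelve "patients who begin the rehabilitation program at the same time complete five specific additional cognitive-behavioral components together". Table 1 labels four of the five components as group interventions; the psychological sessions are individual. The psychologist "leads the group throughout the rehabilitation and is the primary psychological contact". For exercise, "The primary physiotherapist leads the group exercise sessions throughout rehabilitation".

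**Delivery of the control.** The section on standard cardiac rehabilitation gives the treatment standard and the four-week duration. It does not say whether control patients are treated in fixed groups.

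**Sample size.** The target difference is fixed where "we defined 0.2 points of the total cardiac anxiety score", with a standard deviation of 0.6. Then: "To detect this difference with a two-sided error of 5% and a power of 80%, 286 participants are required". A 70% response leads to 410 recruits, and about 92% power is claimed for the primary analysis with imputation. No ICC, design effect or number of groups appears.

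**Model.** Statistical methods reserves mixed models for outcomes with more than one measurement point (end of rehabilitation and 3 months), "and generalized linear models otherwise". The 12-month primary outcome has one measurement point, so it gets a generalized linear model with the baseline score as covariate.

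**The concern.** This is individual randomization followed by treatment in groups in at least one arm. Patients who share therapists, sessions and fellow patients for four weeks may end up with more similar outcomes than patients drawn at random. The primary outcome is self-reported cardiac anxiety, which the group therapy is meant to change, so some positive correlation is plausible.

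The stated model rule looks at repeated measurements and not at treatment groups, so it leads to a primary analysis without any allowance for this dependence. An ignored positive correlation errs in one direction: standard errors and p-values too small, intervals too narrow, power overstated. That favors declaring the new program effective, in a trial whose Discussion says it will inform pension insurers about implementation across Germany. The same reasoning applies to the other outcomes.

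**Working it through.** **1. Reproduce the plan's figures.** Inputs from Sample size: difference 0.2, SD 0.6, two-sided 5%, power 80%, response 70%.

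- Standardized difference: 0.2 / 0.6 = 0.33. The two-sample t-test needs 142.2 per arm, rounded up to 143, so 2 × 143 = 286, as stated.
- 286 / 0.70 = 408.6, consistent with 410.
- With 205 per arm, SE = 0.6 × √(2/205) = 0.0593 and power = Φ(0.2/0.0593 − 1.96) = 92.1%, as stated.
- Complete cases: 205 × 0.70 = 143.5 per arm, SE = 0.6 × √(2/143.5) = 0.0708, power 80.6%.

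All of these come from formulas for independent patients, so the figures contain no hidden allowance for clustering.

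**2. Allow for clustering in the intervention arm only.** Let m be the number of analyzed trial patients per group.

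- Variance multiplier in the intervention arm: DE = 1 + (m − 1) × ICC. Control arm: 1.
- True SE / naive SE: k = √((1 + DE)/2).
- Actual type I error of the naive test: 2 × (1 − Φ(1.96/k)).
- Power of a test that uses the correct SE: Φ(0.2/(k × naive SE) − 1.96).

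Worked case, m = 10, ICC = 0.05: DE = 1 + 9 × 0.05 = 1.45; k = √(2.45/2) = 1.107; type I error = 2 × (1 − Φ(1.771)) = 7.7%; SE = 1.107 × 0.0593 = 0.0656; power = Φ(3.05 − 1.96) = 86.2%.

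**3. Range.** The protocol gives neither the ICC nor m, so both are assumptions.

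| Setting | ICC | DE | k | Type I error | Power |
|---|---|---|---|---|---|
| 205 per arm, m = 10 | 0.02 | 1.18 | 1.044 | 6.1% | 89.8% |
| | 0.05 | 1.45 | 1.107 | 7.7% | 86.2% |
| | 0.10 | 1.90 | 1.204 | 10.4% | 80.0% |
| Complete case, 143.5 per arm, m = 7 (10 × 70%) | 0.02 | 1.12 | 1.030 | 5.7% | 78.3% |
| | 0.05 | 1.30 | 1.072 | 6.8% | 75.0% |
| | 0.10 | 1.60 | 1.140 | 8.6% | 69.7% |
| 205 per arm, m = 3.5 | 0.02 | 1.05 | 1.012 | 5.3% | 91.5% |
| | 0.05 | 1.125 | 1.031 | 5.7% | 90.6% |
| | 0.10 | 1.25 | 1.061 | 6.5% | 88.9% |

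A simulation of the naive t-test with 20 groups of 10 against 200 individual controls (20,000 runs per ICC) gave a type I error of 6.2%, 7.9% and 10.5%, in line with the first block.

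**4. Where m = 3.5 comes from.** Study setting gives 30 slots for the program. Assume about 18 months (78 weeks) of intake, judged from registration in June 2022, study completion on 28.02.2025 and the 12-month follow-up, and assume full occupancy. Then 78/4 × 30 = 585 places; 205/585 = 35%, or about 3.5 of every 10 group members. Lower occupancy raises m.

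**5. Baseline adjustment.** The sample size does not credit it. With an assumed baseline correlation of 0.5, the SE is multiplied by √(1 − 0.25) = 0.866. At ICC 0.05, power is then 94% (205 per arm, m = 10) or 86% (complete case, m = 7). This recovers power, but the SE of a model without a group term still ignores whatever clustering remains.

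**The case against.** **The ICC is unknown and may be small.** The outcome is a questionnaire completed 12 months after the group has ended. This stands. A reader might infer that the primary standard error and p-value are too small as a matter of fact; the protocol supports only the conditional statement.

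**Group size is not the number of trial patients per group.** Eight to twelve is the size of the treatment group. Nothing says that every group consists only of trial patients, and the trial is limited to consenting patients from two insurers. Dividing 205 by 12 and by 8 to get 17 to 26 groups assumes that it does. This stands, and at 3.5 per group the inflation is minor.

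**Power of the primary analysis.** It is tempting to read the 78%, 75% and 70% as the trial's power. They belong to the complete-case analysis. On the plan's own basis for the primary analysis, 92% becomes 90%, 86% or 80%, which does not fall below the 80% target in this range. Whether imputation justifies counting all 410 patients is a separate question.

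**Controls.** A reader might infer that controls are not treated in groups. The protocol is silent. The intervention-arm correction follows what is described; grouping among controls would add to it.

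**Detail for an analysis plan.** The article is condensed, and a generalized linear model can carry cluster-robust standard errors. This stands only in part: Statistical methods states when mixed models are used, and treatment group is not among the reasons, while the sample size section lists its inputs and none is for clustering.

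**Conclusion.** The point holds in conditional form. The plan builds shared treatment into the intervention arm, yet both the sample size and the stated 12-month model treat patients as independent. For any ICC above 0 the direction is certain: standard error too small, stated power too high. The size is not known. Over ICC 0.02 to 0.10, the type I error runs from 6.1% to 10.4% with 10 trial patients per group, but only from 5.3% to 6.5% with 3.5. These figures assume clustering in the intervention arm only, equal group sizes and large-sample critical values.

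The documents do not show that the primary result will be wrong or that the trial is underpowered: baseline adjustment may well make up the lost power, though it does not correct the standard error. Severity: should-fix.

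**What to change.** - **Record now.** Enter an explicit treatment-group number and the lead therapist for each intervention patient in the pseudonymized list. That list already holds the actual start date, but two groups starting together would share one. The study list linking names to identification numbers is to be shredded once all follow-up questionnaires are sent, so this should be done before then. If controls are also treated in fixed groups, record those too.
- **Analysis.** For the 12-month primary and the other outcomes, use a partially nested model (random group effect in the intervention arm only, each control a singleton) or cluster-robust standard errors. Either needs a small-sample correction, because there may be as few as 17 groups if all members are trial patients. Use the logistic analogue for binary outcomes.
- **Imputation.** Carry the group into the chained equations.
- **Power.** Restate it over a range of ICC and of trial patients per group.

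The cost is one or two recorded variables and some analysis wording; no treatment procedure changes. The downside is slightly wider intervals and a less favorable stated power.
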